#### **Safety end points**

Change in hemoglobin concentration within 7 days of start of treatment in PQ compared to the no PQ arm. Hemoglobin concentration will be assessed on day 0, 3, 7, 14, 28, 42. All adverse events will be documented. The proportion of participants with solicited and unsolicited adverse events, overall and specific, will be compared between treatment arms. Events will be analysed in relation to time of the drug administration.

The classification of treatment outcomes will be based on an assessment of the parasitological and clinical outcome of antimalarial treatment according to the latest guidelines from WHO [41].

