## OBJECTIVES

To assess the therapeutic efficacy of AL compared to AL+PQ and CQ compared to CQ+PQ for *P. vivax* infection and to determine the number of recurrent vivax episodes in patients receiving PQ compared to those who don't receive PQ.

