### Specific Objectives

#### Phase 1:

- 1) **Efficacy:** To measure the clinical and parasitological efficacy of AL, CQ, AL+PQ, or CQ+PQ for *P. vivax* infection during a 42-day follow-up period. (See Annex I for WHO definitions of *P. vivax* treatment failures)
- 2) **Safety:** To compare changes in hemoglobin concentration following vivax infection in patients receiving PQ versus patients who don't receive PQ.

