**Sampling, sample size and statistical power****Sample size determination:**

The design of the study is to compare the addition of PQ to AL or CQ alone. From our previous efficacy study, CQ alone showed a success rate of 68% at day 42 (null hypothesis). It will be assumed under the alternative hypothesis that the addition of PQ will decrease the chance of relapse by at least 60% resulting in a success rate of 87%. Group sample sizes of 97 in each group will achieve 90% power to detect a difference between group proportions of 19% using the two-sided Z-test with pooled variance test statistic. The significance level of the test was targeted at 0.05. Adjusting the alpha level to 0.025 for multiple comparisons will increase the sample size to 118 in each group. The AL arm showed even a lower efficacy at day 42 in our previous study of 58%. Using this lower success rate of 58% seen with AL at day 42, resulted in a smaller required sample size of 68. Taking into account 10-20% loss to follow-up at 42 days, a sample size of 120 subjects for each treatment was determined to be optimal.

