### **Laboratory Evaluations:**

2. Urine pregnancy test will be conducted on all women aged 13-49 and anyone testing positive will be excluded.
3. Those enrolled will have a second finger prick performed to assess for the following:
  - Thin smear will be used to verify parasite species and thick smear to conduct a formal parasite count. Two qualified microscopists will read all the slides independently. Blood smears with discordant results (differences between the two microscopists in species diagnosis, in parasite density of > 50% or in the presence of parasites) will be re-examined by a third, independent microscopist, and parasite density will be calculated by averaging the two closest counts.
  - Hemoglobin measurement (HemoCue™ Hb 301HemoCue, Angelholm, Sweden) will be carried out and those with hemoglobin <8g/dL will be excluded.
  - Filter paper will be obtained for the purpose of genotyping to differentiate identical vs. different genotypes, potential molecular testing for resistance markers, and gametocyte testing. G6PD testing using the NADPH fluorescent spot test will be conducted at the end of each day. The NADPH fluorescent spot test is a qualitative test and those determined to be G6PD deficient will not be given primaquine.
4. Patients testing smear positive for Pv will receive AL, at one site and CQ at the other site. After G6PD testing results are available, the patients not found to be G6PD deficient will be randomized to either AL alone or AL+PQ at one study site and CQ alone or CQ+PQ at the other site. Those found to be G6PD deficient will remain in either the AL or CQ alone arms. The study will not be blinded, although microscopists reading blood films will not be aware of which arm a participant is from.
5. On day 0, each patient will receive the morning dose of treatment (AL or CQ) medication under direct observation and will be monitored for vomiting for 60 minutes. The patient or parent will be given the evening dose (for AL only) to administer at home. Each patient will return on days 1 and 2 (and up to 14 days for those in the PQ arms) for subsequent doses. Those in the primaquine arms will return on every second day on days 2-16 for directly observed therapy. Clinical reassessments will be made on days 1- 3, 7, 14, 21, 28, 35, 42, and then monthly (see Annex V and VI for a table of scheduled procedures).

Participants will be given 35 Ethiopian Birr for each visit to cover their travel expenses (this is

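### The haemoglobin endpoint is one PQ versus no-PQ contrast, and recurrence is worded both ways, although PQ is randomised within drug and site

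*Protocol*

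**What the plan says.** **Randomisation.** The Protocol, Laboratory Evaluations, gives AL at one site and CQ at the other. Patients who are not G6PD deficient are then "randomized to either AL alone or AL+PQ at one study site and CQ alone or CQ+PQ at the other site". The section Intervention or treatment says instead that all patients are randomised between AL and CQ. In both versions PQ is randomised afterwards.

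**Haemoglobin.** The Phase 1 safety objective is "To compare changes in hemoglobin concentration following vivax infection in patients receiving PQ versus patients who don't receive PQ". The endpoint under Safety end points is "Change in hemoglobin concentration within 7 days of start of treatment in PQ compared to the no PQ arm". Neither names a drug pair, and the endpoint speaks of its comparator in the singular.

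**Recurrence.** The general Objectives paragraph opens with the two drug pairs and then continues "to determine the number of recurrent vivax episodes in patients receiving PQ compared to those who don't receive PQ". The Phase 2 objective likewise names both pairs and then, in the same sentence, contrasts all PQ patients with all others. Study Design says that relapses are compared between arms.

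**Primary outcome and analysis.** Efficacy end points compares AL with AL+PQ and CQ with CQ+PQ at day 28/42. The data analysis plan reports treatment failures per arm, and side effects and anaemia by arm. For haemoglobin change and number of recurrent episodes it lists a comparison without stating the groups.

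**The concern.** The randomised PQ comparison exists within each drug/site stratum, and the primary outcome respects that. The haemoglobin endpoint does not. Read literally, it sets all PQ patients from both sites against a mixture of AL-alone patients from one site and CQ-alone patients from the other.

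Two things are at stake. First, a single pooled figure does not show whether the PQ effect on haemoglobin is the same with each partner drug. The protocol gives a reason to ask: its section on known adverse effects lists anaemia among the most common events with AL and names no haematological effect for CQ. Second, if the analysis ignores the stratum, differences between strata stay in the error term. The test becomes conservative, which for a safety endpoint makes a real fall easier to miss.

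The groups that an endpoint compares are fixed in the protocol. An SAP author could follow the pooled wording or the pairwise wording and claim support for either.

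**Working it through.** **1. The plan's own sample sizes.** Formula for two proportions, two-sided with pooled variance: n = [z(α/2)·√(2p̄q̄) + z(β)·√(p1q1 + p2q2)]² / (p1 − p2)². Inputs come from the sample size section: 90% power, a CQ success rate of 68%, an AL success rate of 58%, and a 60% cut in relapse.
- CQ pair, α 0.05, 0.68 vs 0.872 (unrounded): (1.1556 + 0.7353)² / 0.192² = 97. This matches "Group sample sizes of 97 in each group will achieve 90% power". The rounded 0.87 gives 100.
- CQ pair, α 0.025, 0.68 vs 0.87: (1.3237 + 0.7370)² / 0.19² = 117.6, so 118, as stated.
- AL pair, α 0.05, 0.58 vs 0.83: (1.2641 + 0.7949)² / 0.25² = 67.8, so 68, as stated.

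The figures reproduce. Each is for one drug pair, and the section considers a lower α for multiple comparisons, so the trial was sized pairwise.

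**2. Haemoglobin change.** Take 120 per arm in each of two strata. Let σ be the SD within a stratum, and let the strata differ in mean *change* by dσ. The protocol gives neither σ nor d, so both are assumptions. A pooled comparison that ignores the stratum estimates the variance as σ²(1 + d²/4), whereas the design needs σ². Information lost is 480 × [1 − 1/(1 + d²/4)].

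| d | excess variance | patients' information lost, of 480 |
|---|---|---|
| 0.3 | 2% | 11 |
| 0.5 | 6% | 28 |
| 0.8 | 16% | 66 |
| 1.0 | 25% | 96 |

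True type I error at nominal 5% is 2Φ(−1.96·√(1 + d²/4)), or 4.3% at d = 0.5 and 2.8% at d = 1. A simulation of 20,000 trials at d = 1 gave 3.1%.

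Power for a 0.25 SD fall uses SE = √(2/240) = 0.0913 SD:
- stratified: Φ(2.739 − 1.960) = 78%
- unstratified, d = 0.5: Φ(2.739 − 2.020) = 76%
- unstratified, d = 1: Φ(2.739 − 2.191) = 71%

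At an assumed σ of 1.5 g/dL, the 95% half-width is 1.96 × 1.5 × √(2/120) = 0.380 for one pair and 1.96 × 1.5 × √(2/240) = 0.268 for the stratified overall effect. The unstratified overall effect at d = 1 has 0.268 × √1.25 = 0.300.

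**3. Twelve-month recurrence counts.** Assume Poisson counts within each stratum, a mean of 1.5 episodes per year without PQ, and the plan's 60% reduction (mean 0.6 with PQ). The variance of the log rate ratio is proportional to 1/1.5 + 1/0.6 = 2.333. Ignoring the stratum adds 2 × [(r2 − r1)/(r2 + r1)]², where r1 and r2 are the two stratum rates.
- Ratio 1.31 (the protocol's day-42 failure rates, 42/32): 0.036/2.333 = 1.5%.
- Ratio 2: 0.222/2.333 = 9.5%.
- Ratio 3: 0.500/2.333 = 21%.

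**4. Day-42 success on the plan's rates** (0.68 to 0.872 and 0.58 to 0.832, 120 per arm).
- SE for the CQ pair: √[(0.2176 + 0.1116)/120] = 0.0524.
- SE for the AL pair: √[(0.2436 + 0.1398)/120] = 0.0565.
- Stratified overall: ½√(0.0524² + 0.0565²) = 0.0385.
- Unstratified overall, 0.63 vs 0.852: √[(0.2331 + 0.1261)/240] = 0.0387.

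The unstratified standard error is 0.4% larger.

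**The case against.** The strongest reply is that no section says drug and site will be ignored. The data analysis plan names no model, and adding a stratum term is commonly left to an SAP. That stands: the loss of precision is conditional. What the SAP cannot settle by itself is the contradiction over which groups are compared.

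A reader might infer that the recurrence analysis also gives no answer by drug pair. The protocol does not support that. The Phase 2 objective names both pairs and Study Design compares arms, so the fault there is mixed wording.

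A reader might also take baseline haemoglobin differences between sites as the source of the loss. For a change score, differences in level cancel, and only a difference in change between strata counts. Values of d near 1 have no support in the document. Differences in level would matter only for the absolute means that the data analysis plan also lists.

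Finally, pooling does not make intervals wide in every sense. The unstratified interval is too wide only against a stratified overall estimate, and a single-pair interval is usually wider still.

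**Conclusion.** The point holds as a defect in the stated comparison. Haemoglobin is fixed as one contrast that does not match the randomisation and promises no result per pair, and recurrence is worded both ways.

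It is tempting to call the pooled contrast biased or invalid, but the documents do not support that. With the planned equal arms of 120 it is essentially unbiased with respect to drug and site, although the allocation ratio itself is not stated. Keeping G6PD-deficient patients in the arms without PQ is a separate matter that affects pooled and pairwise comparisons alike.

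The statistical cost, if the stratum is ignored, is conservatism. The excess variance for haemoglobin change is 2% to 25% for assumed d from 0.3 to 1.0. For the log rate ratio it is about 1.5% at the protocol's own between-drug ratio and 10% to 21% at assumed ratios of 2 to 3. For day-42 success it is negligible. On plausible figures the gain in precision is small. The main reasons to act are the missing per-pair haemoglobin answer and the open choice between pooled and pairwise results.

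**What to change.** Align the Objectives, both Phase objectives, Safety end points and the data analysis plan. State that haemoglobin change and number of recurrences are compared within each drug pair (AL+PQ vs AL; CQ+PQ vs CQ). State that any overall PQ effect is stratified by drug and site: a stratum term in the haemoglobin model and a stratified rate ratio for recurrences. Report both pair estimates beside it.

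Reconcile Intervention or treatment with Laboratory Evaluations on whether AL and CQ are randomised or assigned by site, because the stratum is undefined until that is settled. Treat any replacement site, which Study Sites allows, as a further stratum.

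The cost is a sentence of wording and one model term. No new data are needed, since drug and site are known for every patient. The price of the pairwise results is width: 0.380 against 0.268 g/dL for the stratified overall effect, at an assumed SD of 1.5 g/dL. That is why both should be reported.

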## Definition of Treatment Outcomes for *P. vivax* infections, WHO 2002 [42]

Outcomes defined as:

### For Primaquine:

- Number of vivax episodes following initial parasite clearance during the follow-up period.

### For artemether-lumefantrine or chloroquine:

#### **Early treatment failure**

- danger signs or severe malaria on day 1, 2 or 3 in the presence of parasitaemia;
- parasitaemia on day 2 higher than on day 0, irrespective of axillary temperature;
- parasitaemia on day 3 with axillary temperature  $\geq 37.5$  °C;
- parasitaemia on day 3  $\geq 25\%$  of count on day 0.

#### **Late treatment failure**

##### **Late clinical failure**

- danger signs or severe malaria in the presence of parasitaemia on any day between day 4 and day 28 (day 42) in patients who did not previously meet any of the criteria of early treatment failure;
- presence of parasitaemia on any day between day 4 and day 28 (day 42) with axillary temperature  $\geq 37.5$  °C (or history of fever) in patients who did not previously meet any of the criteria of early treatment failure

##### **Late parasitological failure**

- presence of parasitaemia on any day between day 7 and day 28 (day 42) with axillary temperature  $< 37.5$  °C in patients who did not previously meet any of the criteria of early treatment failure or late clinical failure

##### **Adequate clinical and parasitological response**

- absence of parasitaemia on day 28 (day 42), irrespective of axillary temperature, in patients who did not previously meet any of the criteria of early treatment failure, late clinical failure or late parasitological failure

*P. vivax* infections that recur after drug treatment can have 1 of 3 etiologies: 1) recrudescence, 2) reinfection, or 3) relapse arising from the dormant liver stage (hypnozoites). In order to differentiate the recurrent parasitemias as identical vs. different from the original infection, a genotypic analysis will be performed by PCR including characterizing microsatellite markers to assess recrudescence from reinfection and for drug resistance markers. Molecular testing for gametocytes will also be conducted on any smear positive days. Those who fail in the chloroquine arm will have CQ levels tested from the already collected filter paper. Lumefantrine level on day 7 will be measured for those receiving AL treatment from collected filter papers. Patients noted to have G6PD deficiency by the fluorescent spot test and those with hemoglobin drop of >2.4g/dL will undergo additional G6PD genotyping.

**Valid end-points** include treatment failure, completion of the follow-up period without treatment failure, loss to follow-up, withdrawal from study (voluntary or involuntary, and protocol violation). Loss to follow-up occurs when, despite all reasonable effort, an enrolled patient who does not attend the scheduled visits, cannot be found. Patients who withdraw from the study during the treatment period (days 0-2) will be treated with CQ according to the national policy. They will be referred back to the clinic to continue with care.

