*P. vivax* unlike *P. falciparum* has a dormant stage [hypnozoites] that can persist in the liver and cause relapses by invading the bloodstream weeks, or even years later. Both CQ and AL treat only the *P. vivax* blood stage parasites, resulting in a short-term clinical cure, but these medicines do not eliminate the liver stage infection, leaving the patient at risk of later malaria illness relapses. In a study conducted in Ethiopia in 2009, CQ and AL treatments both caused clinical cures of *P. vivax* malaria lasting up to three weeks in all patients; however, unacceptably high rates of recurrent *P. vivax* parasitemia were noted at 42 days of follow-up, with 41.6% (47/113) in the AL arm and 34% (34/107) in the CQ arm (unpublished data). Many of these recurrent malaria parasitemias were likely caused by relapses of dormant infections, although some probably were from new *P. vivax* re-infections. *P. vivax* infection is ideally treated with either CQ or AL resulting in a clinical cure, then with primaquine (PQ) resulting in a radical cure by eliminating the dormant liver hypnozoite forms. Primaquine radical cure is the standard of care in malaria-free areas such as the United States to prevent relapses and primaquine is the recommended WHO policy for adequate Pv treatment [2].

One study assessing the efficacy of CQ vs. AL both given with primaquine noted cure rates of 97.4% for AL vs. 100% for CQ at day 28 in Thailand [31]. In Ethiopia, the addition of primaquine to CQ decreased the cumulative incidence of therapeutic failure at day 28 by a life-table analysis method from 5.76% to 0.75% and the cumulative risk of relapse at day 157 by a life-table method from 61.8% to 26.3% [32].

Primaquine was previously widely used in Ethiopia according to national malaria treatment guidelines until the late 1990's. However, due to G6PD-related safety concerns that were mostly reported in other countries, primaquine use is now limited to Ethiopian health facilities with good laboratory capacity in non-malarious areas typically located above 2000m altitude. There is currently limited G6PD testing capacity in Ethiopia. The Ethiopian national malaria program is very interested in gathering credible evidence to support the scale up and safe deployment of primaquine for *P. vivax* treatment as the country moves towards malaria elimination.

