## STUDY DESIGN

This trial is a randomised, open label evaluation of clinical and parasitological responses to directly observed treatment for uncomplicated *P. vivax* malaria. Patients with uncomplicated *P. vivax* malaria infection who meet the study inclusion criteria will be enrolled, randomised, and treated on site with either AL or CQ with or without PQ, and monitored for 12 months. The drug administration will be directly observed. The follow-up will consist of a fixed schedule of check-up visits and corresponding clinical and laboratory examinations. On the basis of the results of these assessments, the number of adverse events and number of relapses will be compared between the study arms.

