## DATA HANDLING AND ANALYSIS

### **Data analysis plan, including statistical methodology and planned tables and figures**

SAS 9.3 (Cary, NC) as well as the WHO drug efficacy tools provided at <http://www.who.int/malaria/toolsformonitoring.html> will be used for data management and analysis. Data will be analyzed using two methods: **per protocol analysis**, where patients who were withdrawn from the study or who were lost to follow-up are excluded, and **survival analysis**, where all enrolled patients are included in the analysis until the last day before drop-out. In addition to voluntary withdrawals or treatment non-compliance, patients will be considered for the analysis as withdrawn if the PCR results are unclassifiable.

The final analysis will include:

- A description of the patients screened, and the distribution of the reasons for exclusion.
- A description of the patients included in the study.
- The proportion of patients lost to follow-up or withdrawn and the distribution of reasons for withdrawal.
- The proportion of treatment failures in each Pv arm at day 28 and day 42 with 95% confidence intervals using both methods of analysis.
- Frequency of side effects, severe malaria, anemia, and hospitalizations by treatment arm.
- Comparison in absolute means and relative changes in hemoglobin concentration during follow-up after treatment
- Comparison of number of recurrent parasitological vivax episodes after initial parasite episode.

**Data collection:** Data will be collected and recorded at the health facility by one of the trained staff members. All data entry forms will be checked for completeness. Laboratorians may complete brief reports on laboratory findings to share with clinicians who will transfer these results to the case report form of the appropriate patient, the laboratory results will be entered into an Excel database.

**Information management and analysis software:** Microsoft Excel (Redmond, Washington) will be used for double entry of laboratory data and clinical data. SAS 9.3 (Cary, NC) will be used for data analysis.

**Data entry, editing, handling, storage and disposition:** Some open-ended data including the names of specific drugs or diagnoses will be coded prior to data entry. A list of standard codes for these fields will be developed by hand once collection of data is complete. All forms will then be coded and checked by 2 different team members.

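### Genotyping is meant to separate recrudescence from reinfection but cannot identify relapse, and the unclassifiable-PCR rule removes only patients who recurred from the failure analysis

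*Protocol*

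**What the plan says.** Four places in the protocol bear on this.

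- **End-points, under Adequate clinical and parasitological response.** Recurrences after treatment "can have 1 of 3 etiologies: 1) recrudescence, 2) reinfection, or 3) relapse arising from the dormant liver stage (hypnozoites". The next sentence gives the output of the genotyping, "In order to differentiate the recurrent parasitemias as identical vs. different from the original infection", and its purpose: "a genotypic analysis will be performed by PCR including characterizing microsatellite markers to assess recrudescence from reinfection and for drug resistance markers".
- **Study Design.** It promises that "the number of adverse events and number of relapses will be compared between the study arms".
- **Introduction.** On the earlier Ethiopian study: "Many of these recurrent malaria parasitemias were likely caused by relapses of dormant infections". Some of the others were thought to be new infections.
- **Data analysis plan.** The per-protocol analysis excludes withdrawn patients, and "patients will be considered for the analysis as withdrawn if the PCR results are unclassifiable".

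The outcome definitions carry no genotype condition. Late clinical and late parasitological failure are parasitaemia within the window, with or without fever. The primaquine outcome is the number of vivax episodes after clearance (End-points and Annex I). Any vivax parasitaemia in the year after clearance is a recurrence (Efficacy end points).

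**The concern.** A two-valued test cannot separate three causes. Relapse is the event primaquine is given to prevent, and the sample size assumes a 60% reduction in it, yet relapse has no result of its own. A relapse may match the day-0 genotype or differ from it, so neither result identifies it. The relapse comparison promised under Study Design has no measurement behind it.

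The second problem is how PCR reaches the analysis. If outcomes ignore genotype, an unreadable genotype should not affect whether a patient counts as a failure. The withdrawal rule nevertheless makes it do so. The protocol does not define unclassifiable, and a scheme that offers only recrudescence and reinfection leaves unclear whether a suspected relapse is classifiable at all. At stake are the day-28 and day-42 failure proportions, which are meant to inform national policy on AL and CQ, and the power of the primaquine comparison.

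**Working it through.** **1. The plan's own figures.** With the two-sided pooled-variance Z-test at 90% power, the stated group sizes reproduce: 97 (CQ, success 0.68 vs 0.872, alpha 0.05, where 0.872 = 1 − 0.32 × 0.4), 118 (CQ, 0.68 vs 0.87, alpha 0.025) and 68 (AL, 0.58 vs 0.83, alpha 0.05). No sample-size figure is in dispute.

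**2. Does genotype enter an outcome definition?** No. Early failure, late failure, adequate response, the primaquine outcome and the one-year recurrence all rest on parasitaemia and clinical signs. The planned outputs are failure proportions at days 28 and 42 and the number of recurrent episodes; none is PCR-corrected. The sample-size success rates (68% and 58%) agree with the all-recurrence counts in the Introduction: 1 − 34/107 = 68.2% and 1 − 47/113 = 58.4%.

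**3. Who can have an unclassifiable PCR?** Under Molecular testing, filter paper is taken on day 0 and, after day 3, in case of recurrent parasitaemia. Identical or different needs both samples. A patient who stays clear has no pair to classify, so in practice the rule reaches only patients who recurred.

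**4. Effect on the per-protocol comparison.** Inputs from the protocol: failure 32% on CQ alone (1 − 0.68) and 13% on CQ+PQ (1 − 0.87), 120 per arm, alpha 0.025. Assumptions: all 120 are otherwise evaluable, and the unclassifiable share u of recurrences is the same in both arms. The protocol gives no u, so a range is shown.

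- Removed per arm = 120 × p × u
- Remaining n′ = 120 × (1 − p × u)
- Apparent failure p′ = p(1 − u) / (1 − p × u)
- Power = Φ[(|p₁′ − p₂′| − 2.2414 × SE₀) / SE₁], where SE₀ uses the pooled proportion and SE₁ the separate proportions

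| u | Removed, CQ / CQ+PQ | Remaining | Apparent failure, CQ / CQ+PQ | Difference (points) | Power |
|---|---|---|---|---|---|
| 0 | 0 / 0 | 120 / 120 | 32.0% / 13.0% | 19.0 | 91% |
| 0.1 | 3.8 / 1.6 | 116.2 / 118.4 | 29.8% / 11.9% | 17.9 | 88% |
| 0.3 | 11.5 / 4.7 | 108.5 / 115.3 | 24.8% / 9.5% | 15.3 | 79% |
| 0.5 | 19.2 / 7.8 | 100.8 / 112.2 | 19.0% / 7.0% | 12.1 | 66% |

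Example at u = 0.3, CQ alone: 120 × 0.32 × 0.3 = 11.5 removed; 0.32 × 0.7 / (1 − 0.096) = 0.248. Power: (0.1531 − 2.2414 × 0.0501) / 0.0496 = 0.82, and Φ(0.82) = 0.79.

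More patients leave the CQ-alone arm even with equal laboratory performance, because more of them recur. The failure ratio moves little (13.0/32.0 = 0.41 at u = 0; 7.0/19.0 = 0.37 at u = 0.5). The damage is mainly to the absolute proportions, the difference and the power. In the survival analysis, a patient treated as withdrawn would be censored instead of counted as an event. That effect is not sized here.

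**The case against.** The strongest reply is that the outcomes are genotype-blind. Relapses count as failures and recurrences, so the primaquine effect is captured whatever the genotyping shows. The output is described neutrally as identical or different here, under Laboratory Evaluations and in the material transfer agreement, and how it is tabulated could be left to an analysis plan. All of this stands, and it limits the point.

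It also disposes of a stronger reading. A reader might infer that identical recurrences will be reported as AL or CQ failure, that different ones will be discarded as new infections, and that the trial thereby loses much of its power. If only identical recurrences counted as failures, and 80%, 50% or 20% of recurrences were identical, power would fall to 80%, 54% or 21% for CQ and 93%, 70% or 28% for AL. The arithmetic is right, but it describes an analysis the protocol does not plan. No text maps identical to drug failure or different to non-failure, and no recrudescence rate is among the objectives or listed outputs. Chloroquine levels at recurrence and day-7 lumefantrine levels give other evidence on blood-stage failure.

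Two things survive the reply. The stated purpose omits a cause named in the sentence before it. And the withdrawal rule is an explicit instruction in the protocol that conflicts with the genotype-blind definitions; it is not a detail left open for later.

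**Conclusion.** The point holds in a limited form. The genotyping cannot do what the protocol says it is for when relapse is possible, and it cannot supply the promised number of relapses. The primary and 12-month outcomes remain valid for primaquine as defined, and the documents do not support a claim that the AL or CQ conclusion would be wrong. Nor do they support more than this about relapse frequency: the Introduction says many recurrences were likely relapses, without a share.

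The documented harm is the withdrawal of patients with unclassifiable PCR. At an assumed 10% to 50% of recurrences, apparent CQ-alone failure drops from 32% to between about 30% and 19%, and power from 91% to between about 88% and 66%. These sizes rest on the assumed share, an equal share in both arms, and 120 evaluable patients per arm. The direction does not depend on the size of the share: any nonzero one lowers the apparent failure proportion. The correction should be made; it is cheap and improves the failure estimate.

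**What to change.** - **End-points, aetiology paragraph:** delete the clause giving the purpose of genotyping as telling recrudescence from reinfection. Report genotype by arm only as identical to or different from day 0, as a descriptive table beside the day of recurrence and the drug levels already collected. State that neither class identifies recrudescence, reinfection or relapse.
- **Study Design:** promise a comparison of the number of recurrences in place of the number of relapses.
- **Data analysis plan:** delete the sentence part that treats unclassifiable PCR as withdrawal. State that day-28 and day-42 failure and the 12-month count use all slide-confirmed vivax recurrences without genotype correction. Both changes are needed: adding the statement while keeping the withdrawal rule would leave the protocol contradicting itself.

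The cost is a few sentences of wording, with no new samples, tests or patients. The one thing given up is a PCR-corrected cure rate for AL or CQ, which the protocol does not define in any case.
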